### Substudies

Substudies of ZIKV viral kinetics, clustering of ZIKV transmission, impact on disability and health economics, the potential role of antibody enhancement, and co-infections will be connected to the NH and PW cohort studies (Fig. 1). ZIKV transmission occurs mainly through the bite of an infected female *Aedes* mosquito [47], but transmission through blood transfusion [55–57], sexual intercourse [58–65] and direct contact through intact skin [66] have also been reported. ZIKV shedding seems to occur in a range of body fluids, most notably in male genital fluids where shedding can be protracted for months [64, 67]. Some reports also suggest shedding can also be prolonged in PW [27, 68, 69]. The frequency and duration of ZIKV shedding in different body fluids is unknown, as is the significance of viral shedding for the risk of person-to-person transmission.

#### Seroprevalence studies in communities

Estimates of ZIKV incidence in affected areas are often based on notifications with insufficient laboratory confirmation resulting in misclassifications due to other circulating arboviruses [44]. Seroprevalence studies in communities representing the epidemiological context of potential participants will be underway to guide the selection and potential relocation of sites for ZIKAlliance cohorts over the course of the study. Populations under investigation include groups representing a range of socioeconomic status, environmental exposure and susceptibility to viral sexual transmission.

#### Viral kinetics substudy

This substudy will enrol adults with PCR-confirmed ZIKV identified in the cohorts in selected sites who consent with a more intense follow-up including genital samples if possible. Scheduled visits occur at days 7, 14, 21 and 28 after inclusion, then months 3, 6 and 12, with additional collection of samples until no ZIKV is detected in any sample. The primary outcome will be the frequency and duration of ZIKV detection in blood and other body fluids (saliva, urine, genital secretions, breast milk) for 12 months following acute ZIKV infection, and secondary outcomes will include potential associations with clinical manifestations and long-term complications or sequelae.

#### Household substudy

Household (HH) contacts of PW or NH participants with confirmed ZIKV infection will be invited to participate in in selected study sites. The main objective is to compare the prevalence of ZIKV infection in well-defined groups, using RT-PCR in blood and urine samples, as well as serological methods. Of special interest is the ratio of the markers of ZIKV infection between sexual partners compared to other HH contacts. In virologically-confirmed patients, we will conduct phylogenetic analysis to establish potential concordance of ZIKV strains within and between HH. HH contacts will be defined as any person aged 5 years and older spending > 1 week in the same HH within 1 month of the index patient being identified.

#### Disability and health economics substudies

We will describe medium-term complications and disabilities among ZIKV patients following acute infection, and the impact of ZIKV infection on health, quality of life and disability. We will estimate the socio-economic burden of the disease in terms of use of family resources, loss of income and leisure time.

### Laboratory support to studies

In order to ensure comparability of inclusions across the sites, protocols, facilities, and capacity for virologic and serological testing will be assessed for the laboratories linked to the clinical centres. Initial molecular testing as well as IgM/G serology will be done locally, with proficiency testing provided through the project. For molecular testing, locally available protocols will be used. Laboratories with insufficient performance in the External Quality Assurance (EQA) testing are supported by laboratory partners in the project for troubleshooting and confirmatory testing.

Molecular testing is the gold standard for ZIKV diagnosis and is definitive evidence for infection. Laboratory testing will be carried out using RT-PCR (in plasma/serum, urine, and other body fluids for ZIKV) and serology (serum/plasma). An initial inventory of essential diagnostic capacity of the laboratories associated with clinical sites was performed, based on a previously developed laboratory capacity and capability survey for ZIKV diagnostics [70, 71]. Standards have been prepared for molecular diagnostic testing [72, 73]. EQA for molecular detection of ZIKV was carried out at the start of the study, and will be repeated at regular intervals [74]. Should lack of sensitivity be noted, the site will be contacted, and test algorithms revisited, including changes in assays or protocols. In order to harmonize laboratory procedures, detailed standardized laboratory protocols were developed describing the sampling frame, sample volumes, shipping and storage conditions.

Several serological assays measuring anti-Zika virus IgM and IgG are commercially available. From the beginning of this study, all sites have been using such assays, for which sensitivity and specificity estimates have ranged from 88 to 95% and 30–98%, respectively [75]. The highest estimates were generated in targeted evaluation studies during the peak outbreak phase, and in regions with a lower background frequency of prior flavivirus exposure. The choice of the assays will be re-evaluated on a continuous basis and may be adapted according to new developments.

At enrolment, all participants of the PW cohort will be tested for IgG (ZIKV, DENV) and IgM (ZIKV) antibodies as well as via RT-PCR (as mentioned). Previous flavivirus infection status as well as vaccinations, if applicable (i.e. against YF or DENV) will be assessed as potential risk factors. In the case that other (arbo) viruses emerge in a certain location, they will be included in the testing panels. Positive PCR results will be repeated for confirmation including RNA extraction, unless both urine and blood are tested positive initially. IgG and IgM will be repeated at birth. Additional tests (e.g. serology) will be carried out either batched or individually, also depending on the laboratory capacities at each location. In the event of confirmed seroconversion at birth, retrospective testing of samples will be carried out for identification of timing of infection during pregnancy. Serologic tests will be performed using the approved, commercial kits and in the designated laboratories in each country. ZIKV IgM will be tested once every trimester of pregnancy as these antibodies may be short-lived. The best frequency for ZIKV IgM testing will still be subject to validation. In a subset of PW residing in an area with documented ZIKV transmission in the previous season with detectable anti-ZIKV IgG at enrolment, we will evaluate the specificity of the IgG assay by confirmatory virus neutralisation (VNT) assays with ZIKV and DENV and other ZIKV specific serological assays, performed in a reference laboratory. Results of the VNT and other assays may trigger adaptations of the follow-up schedule (e.g. for women who are no longer under risk of ZIKV infection).

Routine laboratory facilities in each participating site will be engaged in performing laboratory tests such as full blood count or biochemistry. TORCHS and HIV screening are part of the routine health investigations of PW in many countries. Where this is not available, TORCHS and HIV screening will be performed in samples from all mothers who have experienced adverse pregnancy outcomes or where congenital abnormalities are documented. In addition, a laboratory capacity strengthening program will be done in liaison with other consortia, and with an European network of diagnostic virology laboratories [70, 71, 73].

**Box 4** Diagnostics used in the ZIKAlliance studies

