#### Study design

Screening of PW will take place in routine antenatal care clinics in selected sites in Latin America and the Caribbean. PW will be enrolled regardless of ZIKV symptoms at baseline.

PW will be followed over the course of the pregnancy approximately every 4 weeks making use of routine antenatal care visits and revisited at delivery (or after miscarriage/abortion) with assessment of rash/fever illness episodes and collection of serial blood/urine samples. Investigations will also include a comprehensive assessment of potential co-factors or effect modifiers for the risk of congenital malformations in ZIKV-infected PW, such as demographics, socio-economic status, living conditions, TORCHS infections (Toxoplasmosis, Rubella, Cytomegalovirus, Herpes and Syphilis; to be tested in a subset and according to national guidelines), HIV serostatus, previous flavivirus infections or vaccines (e.g. DENV or yellow fever [YF]), environmental toxins, and chromosomal abnormalities. Symptomatic infections with other arboviruses (including, but not limited to DENV, Chikungunya [CHIKV], YF, Mayaro, Oropouche) during pregnancy will also be evaluated as possible co-factors. PW with suspected or confirmed ZIKV infection will be managed according to national protocols.

The visit at birth will be considered the last visit in the PW cohort and the starting point for the CH cohort. Samples from placenta, amniotic fluid, cord blood, maternal blood and urine and blood from the infant will be collected at the birth visit. All newborns will receive a detailed examination. Any abnormalities will be recorded and evaluated according to the evolving definition of the CZS [32]. Laboratory-confirmed ZIKV infection will be defined based on a positive ZIKV quantitative reverse transcriptase (RT)-PCR in either body fluid or tissue biopsy (e.G. *placenta*). Seroconversion between paired samples collected at different points of time may be considered as a possible recent ZIKV infection. In view of the conflicting evidence on the specificity of currently available serological assays, the final stratification will be based on an exhaustive evaluation of a subset of PW, which will include the use of (combinations of) assays developed to increase discriminatory power for flavivirus antibody testing [33, 34]. Over the course of this study, both laboratory and clinical diagnostic criteria may undergo modifications based on results from this study and others.

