**Table Tabd:** 

**Diagnostics** **Diagnostic approach** The diagnostic approach is subjected to validation over the course of the study. The diagnostic approach includes: - ZIKV RT-PCR in plasma and urine at every visit for PW, CH and NH protocols - ZIKV IgM/IgG at PW enrolment and at birth (and at least one IgM every trimester of pregnancy) - ZIKV IgM/IgG at every visit of the CH cohort (both mother and child) and in paired samples in participants of the NH study - Dengue virus (DENV) IgG at enrolment in a subset (possibly using new platforms and/or VNT for the assessment of past infection status) - RT-PCR for DENV and CHIKV in addition to ZIKV in symptomatic participants **Harmonisation of diagnostics** An EQA for molecular detection of ZIKV was performed at the start of the study and will be repeated at regular intervals to assess the quality of the currently used molecular test systems for ZIKV detection in the ZIKAlliance diagnostic laboratories. This includes: - An inventory of essential diagnostic capacity in the laboratories associated with clinical sites, based on previously developed capacity, and a capability survey for ZIKV diagnostics - Detailed standardized laboratory protocols describing the sampling frame, sample volumes, shipping and storage conditions - Standards have been prepared for molecular diagnostic testing in the laboratories associated with clinical sites in order to assess sensitivity/specificity issues If issues in the precision or accuracy of diagnostic tests are noted, the site is contacted for revision of test algorithms, including changes in assays or protocols.	

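### VNT in women who are all ZIKV IgG-positive gives the positive predictive value of the IgG assay, not the specificity the article says it will evaluate

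*Protocol article*

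**What the plan says.** Under Laboratory support to studies, the protocol article defines the evaluation set: "In a subset of PW residing in an area with documented ZIKV transmission in the previous season with detectable anti-ZIKV IgG at enrolment". The same sentence ties that set to the quantity: "with detectable anti-ZIKV IgG at enrolment, we will evaluate the specificity of the IgG assay by confirmatory virus neutralisation (VNT) assays" against ZIKV and DENV, together with other ZIKV-specific serological assays, in a reference laboratory. The next sentence gives one use of the results: they may change the follow-up schedule, for example for women no longer at risk of infection.

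Three other places bear on this.

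- The same section says that at enrolment "all participants of the PW cohort will be tested for IgG (ZIKV, DENV) and IgM (ZIKV) antibodies", so IgG-negative women are identified across the cohort.
- It also says of commercial ZIKV IgM and IgG assays that "sensitivity and specificity estimates have ranged from 88 to 95% and 30–98%, respectively". Here specificity is plainly the diagnostic-accuracy measure.
- Box 4 (Diagnostics) mentions VNT once more, but for dengue: "Dengue virus (DENV) IgG at enrolment in a subset (possibly using new platforms and/or VNT for the assessment of past infection status".

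No section provides for ZIKV VNT in ZIKV IgG-negative women.

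**The concern.** Specificity is the share of truly unexposed women who test negative. Its denominator is all unexposed women, and most of those are IgG-negative whenever specificity exceeds 50%. If only IgG-positive women are verified, the denominator is the positives, and the proportion obtained answers a different question.

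This is not a detail left out of a condensed article. The article states both the set and the quantity, and the first cannot deliver the second. Improving diagnosis is secondary objective 1 of the pregnant women cohort (Box 1), and the choice of assay is to be re-evaluated throughout the study. A confirmation rate labelled specificity would invite comparison with the 30–98% range, and comparison between sites whose prior exposure differs, when part or all of the difference could come from exposure and not from the assay.

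**Working it through.** The article gives no sample size or estimate for this evaluation, so there is no figure to reproduce. The check is the 2×2 table of IgG (index test) against VNT (reference).

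**Inputs**
- Sensitivity Se: 88–95% in the article; 90% is used below.
- Specificity Sp: 30–98% in the article; 60% is used as a middle value.
- Prior ZIKV exposure π in the evaluated areas: not given. Assumed range 10–70%.
- VNT is taken as a correct reference, and Se and Sp as constant across exposure levels. Both are simplifications.

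**Step 1: what the set identifies**
- Specificity = TN / (TN + FP).
- PPV = TP / (TP + FP).
- In IgG-positive women TN = FN = 0 by design. The first formula would return 0 whenever there is any false positive. Only the second can be estimated.

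**Step 2: PPV at a fixed specificity**

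PPV = Se·π / [Se·π + (1 − Sp)(1 − π)], with Se = 0.90 and Sp = 0.60:

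| Assumed π | Calculation | PPV |
|---|---|---|
| 10% | 0.09 / (0.09 + 0.36) | 20% |
| 30% | 0.27 / (0.27 + 0.28) | 49% |
| 50% | 0.45 / (0.45 + 0.20) | 69% |
| 70% | 0.63 / (0.63 + 0.12) | 84% |

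At Sp = 0.30 and π = 70%, PPV = 0.63 / (0.63 + 0.21) = 75%.

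**Step 3: where PPV and specificity cross**

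Setting PPV = Sp gives π = Sp / (Se + Sp). For Se = 0.90 and Sp = 0.60 this is 0.60 / 1.50 = 40%. Below that exposure the PPV lies under the specificity; above it, over.

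**Step 4: the reverse question**

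Suppose 80% of IgG-positives are confirmed and Se = 0.90. Then Sp = 1 − Se·π(1 − PPV) / [PPV(1 − π)]:

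| Assumed π | Calculation | Implied Sp |
|---|---|---|
| 10% | 1 − 0.018/0.72 | 97.5% |
| 30% | 1 − 0.054/0.56 | 90.4% |
| 50% | 1 − 0.090/0.40 | 77.5% |
| 70% | 1 − 0.126/0.24 | 47.5% |

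One observed figure is compatible with most of the article's own range.

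**Step 5: what the known IgG-positive fraction adds**

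Every woman has an IgG result, so the IgG-positive fraction q is known. With an external sensitivity, π = q·PPV / Se and Sp = 1 − q(1 − PPV) / (1 − π).
- q = 50%, PPV = 50%: π = 0.25/Se. Se = 0.88 gives 1 − 0.25/0.716 = 65.1%; Se = 0.95 gives 1 − 0.25/0.737 = 66.1%.
- q = 80%, PPV = 80%: π = 0.64/Se. Se = 0.88 gives 1 − 0.16/0.273 = 41%; Se = 0.95 gives 1 − 0.16/0.326 = 51%.

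Specificity can therefore be derived, closely in the first case and loosely in the second, but only with an imported sensitivity. The article describes no such step.

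**The case against.** **The sampling fits the use that is stated.** The article says the results may change follow-up of women no longer at risk. That asks whether a positive IgG truly reflects ZIKV, and neutralisation against ZIKV and DENV in IgG-positives is the right test. This stands: for that decision the PPV is the relevant quantity. Specificity might also be meant loosely, as whether the antibody is ZIKV-specific. In that case the laboratory step is sound and the name is wrong. But the same section uses the word beside sensitivity as a percentage, so readers will take it as diagnostic accuracy.

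**A reader might infer that the PPV will overstate the assay, because the subset comes from areas with recent transmission.** The documents do not support this. They give no seroprevalence, and documented transmission in the previous season does not establish high exposure. At 10% and 30% exposure the PPV understates a 60% specificity. The article also says the highest published accuracy estimates came from peak-outbreak evaluations and regions with less prior flavivirus exposure, so specificity itself may vary by setting.

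**A reader might infer that the result determines the final infection grouping.** The Study design section of the pregnant women cohort does say "the final stratification will be based on an exhaustive evaluation of a subset of PW". It does not say that this is the same subset or that it is limited to IgG-positives. Laboratory-confirmed infection there rests on RT-PCR, so the link is possible but not documented.

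**Specificity is not beyond recovery.** Step 5 shows this is correct, given an explicit sensitivity range.

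**Conclusion.** The point holds as a mismatch between the stated evaluation set and the stated quantity. VNT in IgG-positive women alone estimates the PPV. At an assumed sensitivity of 90% and specificity of 60%, that PPV runs from 20% to 84% as assumed prior exposure runs from 10% to 70%, so the error from reading it as specificity can go either way. The exposure range is an assumption; the mismatch itself does not depend on it.

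The consequence is limited to secondary objective 1 and to any comparison of the result with published specificities or between sites. The follow-up decision for IgG-positive women is not undermined, and no effect on the primary analysis is shown.

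**What to change.** Within the VNT subset, include a random sample of ZIKV IgG-negative enrolment sera from the same sites. Estimate specificity and sensitivity with weights for the known IgG-positive and IgG-negative fractions (Begg–Greenes correction). As an illustration, take 1000 women with π = 30%, Se = 90% and Sp = 60%: TP 270, FP 280, FN 30, TN 420. The 550 IgG-positives alone give 270/550 = 49%. With the 450 IgG-negatives represented, specificity is 420/700 = 60% and sensitivity 270/300 = 90%.

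If only IgG-positives can be tested, call the result the PPV and report it by site. Give a specificity only as derived from the site's IgG-positive fraction, with the sensitivity range stated (for example 88–95%).

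Cost: if the subset size is kept, no additional assays, but a less precise PPV; how much less cannot be said, because the subset size is not given. Sera are stored locally and VNT is done in a reference laboratory, so some IgG-negative sera must also be retrieved and shipped. Renaming the measure costs nothing.

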**Table Tabd:** 

**Diagnostics** **Diagnostic approach** The diagnostic approach is subjected to validation over the course of the study. The diagnostic approach includes: - ZIKV RT-PCR in plasma and urine at every visit for PW, CH and NH protocols - ZIKV IgM/IgG at PW enrolment and at birth (and at least one IgM every trimester of pregnancy) - ZIKV IgM/IgG at every visit of the CH cohort (both mother and child) and in paired samples in participants of the NH study - Dengue virus (DENV) IgG at enrolment in a subset (possibly using new platforms and/or VNT for the assessment of past infection status) - RT-PCR for DENV and CHIKV in addition to ZIKV in symptomatic participants **Harmonisation of diagnostics** An EQA for molecular detection of ZIKV was performed at the start of the study and will be repeated at regular intervals to assess the quality of the currently used molecular test systems for ZIKV detection in the ZIKAlliance diagnostic laboratories. This includes: - An inventory of essential diagnostic capacity in the laboratories associated with clinical sites, based on previously developed capacity, and a capability survey for ZIKV diagnostics - Detailed standardized laboratory protocols describing the sampling frame, sample volumes, shipping and storage conditions - Standards have been prepared for molecular diagnostic testing in the laboratories associated with clinical sites in order to assess sensitivity/specificity issues If issues in the precision or accuracy of diagnostic tests are noted, the site is contacted for revision of test algorithms, including changes in assays or protocols.	

### Data management and biobanking

Participants will be assured that all information generated in this study will remain confidential. All data (including clinical, laboratory and genetic data) will be stored in password-protected databases. Personal identifier information will be linked to stored data or samples only by a protected Master List (pseudonymization). This list will be kept under lock locally and will not be shared outside the study staff at the local partner site. No identifying information will be transferred between sites or to the central database. A governance board including members from all partners has been defined to coordinate the use and potential sharing of data and samples.

Electronic web-based case report forms (CRFs) have been developed using REDCap [76]. An electronic data entry interface was set up with the option of online data entry using a tablet device. Patient records will be entered as pseudonymized records (by use of a study identification number), not allowing the personal identification of patients. Clinical data and locally performed laboratory results will be entered directly to the electronic database. If initial data collection is performed in paper CRFs, data entry will be performed in a REDCap electronic CRF that mirrors the layout of the paper form.

Privacy and data safety will be ensured by a secured backup server and restricted access, also accommodating different levels of data access for participant identifiable information. Upon entry, data will automatically be validated across the entire patient record to fit the specific protocol requirements (plausibility and range checks). Data queries and source data verification requests will be generated and relayed back to each participating site for correction. A virtual, decentralized biobank will be created with an inventory of which samples will be available and where, how they will be stored, and what (raw) laboratory data will be associated. Samples will be stored locally, and a governing body created to ensure access and respond to requests for samples. The collection and storage of biological specimens will be regulated by SOP that are accessible to all partners.

